## **21. End of trial and archiving**

### **21.1 Definition of end of trial**

The end of follow-up for each participant is defined as completion of the follow-up visit at 15 months. The end of follow-up is when the last participant completes their follow-up visit at 15 months. The end of the trial is defined as the end of funding (31st March 2027).

The Funder, Sponsor, study team and/or the Trial Steering Committee have the right at any time to terminate the study for administrative or other reasons.

If terminated prematurely, the study team will inform participants and ensure that the appropriate follow up is arranged for all involved.

An end of trial report will also be issued to the funders at the end of funding.

### **21.2 Archiving**

All study documentation will be kept for at least 10 years from the end of the study. Researchers obtaining consent will return consent forms and completed eligibility screening forms (ASSIST-Lite screening tool) to the SHARPS trial office in Stirling where they will be securely stored. If a potential participant did not meet the inclusion criteria (they score below the threshold on the ASSIST-Lite screening tool), all documentation will be shredded on The Salvation Army service premises and not returned to the trial office in Stirling. If electronic data collection is not possible, at the end of each participant's follow-up, Research Assistants will collect the data using paper copies of the questionnaires. Research Assistants are required to input any data they collect using paper copies into the CHaRT data collection tool as soon as the technical issue is resolved. Research Assistants will store any paper copies of anonymised participant data until they have finished collecting the participant data at that timepoint. A courier or tracked delivery will then be arranged to return any paper copies to the University of Stirling for safe storage. Adverse event forms and change of status forms will be completed and returned via email to the study leads at the University of Stirling ([name] and [name] for adverse events and [name] for change of status), or be entered electronically directly onto the SHARPS website database (where the University of Stirling team will be automatically notified by email). Research Assistants and Peer Navigators completing adverse event forms or change of status forms will also inform the study lead ([name]) or Deputy Study Lead ([name]) by phone call that a form has been completed and returned, if there is no response by email after 12 hours. If not captured electronically, once received, all adverse event forms and change of status forms will be recorded in the CHaRT tool by research staff at the University of Stirling. Where appropriate, the study leads at the University of Stirling will follow up with those reporting the incident to ensure that further action has been taken to ensure the safety of those involved. There will be no files stored at the trial sites, all files will either be stored on the SharePoint system, or securely within the University of Stirling or the University of Aberdeen.

Data will be archived by CHaRT for at least 10 years after the end of the study.

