In addition, as per NIHR guidance, we will ask study participants to consent to long-term follow-up (e.g., beyond the outcomes to be collected in the proposed study) using routinely collected data, and appropriate linkage to allow these data to be best used. This activity (long-term follow-up) will not be conducted during this three-year trial but instead it is purely ascertaining consent for such linkage to be conducted at a future point. Participants will be asked about whether or not they consent to data linkage and will be informed that this is optional – they can say no and still be involved in the trial. For those who say yes, basic details to facilitate data linkage in the future will be collected.

As per developing practice around open science, we will also ask intervention and control group participants if they consent to sharing their anonymised data with other researchers in the form of the final quantitative dataset at the end of the study. We must balance the need to ensure recruitment targets are met with this desire to comply with best practice in the field. If client participants are not comfortable with sharing their data, we will revise our plan to do this because it is more important to be sensitive to the needs of this client group. The client group is likely to have had experiences that may make them suspicious of data sharing, despite the commitment to fully anonymising the dataset. We will provide a box on the consent form which indicates that sharing their details via open science will be optional and then the research team will decide about proceeding with the possibility of the open science dataset being shared once all participants are recruited. We will not be sharing the qualitative datasets due to potential small numbers and challenges anonymising the data.

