## **8.2 Control group**

The Salvation Army services within clusters assigned to the control arm will not have Peer Navigators. Instead, participants will receive the local care (standard care) pathway within The Salvation Army services. While standard care within these settings may vary between areas it usually involves having support workers help those attending services with a range of issues for example with housing applications, with contacting relatives, or wider support services. The qualitative process evaluation will systematically describe standard care at baseline, including any variations across all control sites, and any changes over the course of the trial.

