### **12.1 Participants**

It is not expected that serious adverse events will result from taking part in the trial. However, given the vulnerability of people involved in the study, there will be a process for reporting and recording disclosures of current or future intent to harm themselves or others, or situations of actual / potential harm having taken place/at risk of taking place (this will be breaking confidentiality which is detailed on the participant information sheet and consent form for the study).

Most of the adverse events reported in the SHARPS study will be due to responses to a specific question in the PHQ-9 measure of depression which asks about suicidal thoughts or harm to self in the last 2 weeks. When this question is answered with any option other than 'not at all', the researcher is expected to inform staff in the service and complete an adverse events form for the participant. If such disclosures do occur, these will be shared by the researcher with service staff on the day of recruitment/data collection. Service staff will conduct a risk assessment as per their duty of care and The Salvation Army responsibilities. Researchers are not additionally required to verbally discuss such adverse events with the study leads unless they are seriously concerned about a participant's wellbeing.

An adverse events form describing the disclosure and the action taken will be completed by the researcher (with only the participant identifier code being recorded on the form) via the CHaRT data collection tool. These will all be notified electronically via the CHaRT website to the Study lead, Deputy Study Lead and Cluster Lead ([name]/[name]/[name]). They will also be notified by the researcher taking the disclosure to the Study Leads/Cluster Leads (above) via email. At the end of the recruitment/data collection day in service, the designated lead for adverse events (usually [name] but also [name]/[name] as needed) will go onto the study website and sign off on each of the adverse events from that day, checking that actions taken by researchers are appropriate.

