At the end of each recruitment/data collection day in a service, the researchers will report the numbers of participants recruited to the study/who have done data collection to the cluster lead ([name]/[name]) who will then summarise the numbers to the Service Manager/Programme Manager. Any adverse events will be included in this email. The email will note the initials of the participants where there was an adverse event and what staff members were told about this (in line with the above) at the time. The participant initials and year of birth for individuals who have experienced an adverse event related to their response to the PHQ-9 in control service sites will also be reported The Salvation Army Senior Management in order for them to take forward safeguarding processes with control site service managers. There will be no other "more traditional" safety reporting of other adverse events within SHARPS.

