Given that some participants may no longer be supported by The Salvation Army at 6-, 12- and 15-month follow up points, researchers will follow a different adverse events process for these individuals. If the participant reports thoughts of suicide/self-harm in response to the PHQ-9 or other issues, the data collector will remind them that they will have to inform the Study/Cluster leads about the disclosure. The researcher will also provide the participant with information about national/local support resources, including suicide helplines, via an information sheet at the end of the data collection session. The researcher will also tell the participant that a member of the study team will contact them (via phone, text and/or email) within 3 working days. If the data collector believes that the participant is in immediate danger, they will call the Police on 999. The data collector will then complete the usual adverse events form describing the disclosure and the action taken (with only the participant identifier code being recorded on the form) via the CHaRT data collection tool. An identified member of the study team will then contact participants within 3 working days to check in with them, ask them how they are feeling, and remind them of relevant services for support or to contact their GP. Three attempts will be made to contact the participant, if there is no response this will be recorded. The study team member will then log the participant contact and details of the call on a follow up risk assessment log stored on the SharePoint site. Co-investigators with specialist expertise in mental health will review the actions taken for all participants.

Any deaths will be recorded through the Change of Status, including cause and date of death where known.

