## **12.2 Research staff and Peer Navigators**

We will take all reasonable steps to ensure staff safety. Researchers will undertake training including GCP training provided by NIHR, follow clear safety protocols, and should disclose any adverse events (e.g., violence and intimidation) they experience to the study leads and an adverse event form should be completed. All adverse event forms will be entered into the CHaRT data collection tool and stored electronically on the secure SharePoint. Risk assessments will also be conducted for the researchers throughout the study using university procedures. Any issues will be discussed with a member of the study team ([name], [name], [name]). Given the vulnerability of participants in the study, researchers will also be provided with additional training around suicide and reviewed, with additional support provided where required.

Peer Navigators will be provided with support and training around safety. Peer Navigators will be under the line management of The Salvation Army staff and will follow The Salvation Army procedures around adverse events and safeguarding reporting when working within the service. However, given that the role will involve outreach support to clients Peer Navigators should disclose any adverse events or safeguarding concerns they experience (including stalking, violence, intimidation, witnessing a crime, relapse) to their line manager within The Salvation Army immediately as soon as an incident occurs, contact the study leads and an adverse event form should be completed. Peer Navigators will also be encouraged to discuss issues arising from their role (e.g., clients encroaching on or testing boundaries, their own risk of relapse) in line management and clinical supervision. A lone working policy will be in place for Peer Navigators and lone working apps for phones will be provided where this is desirable for the Service Manager/Peer Navigator to have. Research staff will also have a lone working policy and risk assessment in place.

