### Safety

Collected throughout the trial:

- Number and proportion of adverse events
- Number of adverse events per participant
- Details of adverse events including seriousness

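### Between visits, the only named form-completer in regular contact with participants exists in the intervention arm alone, so deaths may be ascertained unequally by arm

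*Protocol*

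**What the plan says.** **Who completes the forms.** Section 21.2 is the only place that names people as completing both adverse event and change-of-status forms: "Research Assistants and Peer Navigators completing adverse event forms or change of status forms will also inform the study lead". Section 8.2 adds that "The Salvation Army services within clusters assigned to the control arm will not have Peer Navigators".

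**Deaths.** Section 12.1: "Any deaths will be recorded through the Change of Status, including cause and date of death where known". On linkage to routine records, section 7.3 says: "This activity (long-term follow-up) will not be conducted during this three-year trial".

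**Adverse events in participants.** Section 12.1 expects one main source: "Most of the adverse events reported in the SHARPS study will be due to responses to a specific question in the PHQ-9 measure of depression". Researchers ask that question in both arms. The same section then says: "There will be no other 'more traditional' safety reporting of other adverse events within SHARPS".

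**Adverse events in staff.** Section 12.2 tells Peer Navigators what to do about events and safeguarding concerns that they experience in outreach work, including to "contact the study leads and an adverse event form should be completed". All adverse event forms go into one data collection tool.

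**The outcome.** Section 13.2 lists, as collected throughout the trial, "Number and proportion of adverse events", the number per participant, and details including seriousness.

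**The concern.** Research Assistants see participants in both arms, but at scheduled assessments. A Peer Navigator works with a caseload of up to 25 people for 12 months and is likely to hear of a death, a move or a crisis when it happens. The protocol gives no control-arm worker the matching task. A control participant who dies between visits may simply be missed at the next window, and loss of contact is itself a ground for withdrawal (7.3 and 10), so an unnoticed death has a ready category to fall into.

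Deaths are the most serious safety information in this population. Safety data go to the steering and data monitoring committees (14.2), and statisticians are left unblinded partly for safety monitoring (7.4). If one arm has better ears than the other, a difference in recorded deaths could reflect reporting and not risk.

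**Working it through.** **1. Denominators.** From 14.1, with 10 clusters per arm: 10 × 25 = 250 intervention and 10 × 30 = 300 control, total 550, as stated. With attrition of 40% and 50%, 250 × 0.60 = 150 and 300 × 0.50 = 150 have outcome data, also as stated. So 100 and 150 are missing. The protocol's power figure concerns the co-primary outcomes. It gives no figure for deaths or harms.

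**2. Who could report between visits, by arm.**
- Research Assistants: both arms, seeing participants at the scheduled assessments (11.1).
- Peer Navigators: intervention arm only, continuous contact, named in 21.2.
- Service, Programme or Project Managers: both arms. Section 7.3 lets them tell a participant that they cannot continue, after which a form is completed. It does not say by whom, and gives them no duty to report deaths.
- Control Support Workers: recruited to complete their own outcome measures (7.1). No participant reporting role.

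Two provisions widen the difference. Intervention participants who move away may keep their Peer Navigator (7.3), with no control counterpart stated. If a cluster's services are decommissioned, the Peer Navigator carries on, while control participants depend on Research Assistants' follow-up attempts (14.7, risk table).

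**3. Size for deaths.** Let the true risk be r in both arms and the probability that a death becomes known be d_I and d_C. Recorded risks are r·d_I and r·d_C, so the recorded risk ratio is d_I/d_C and r cancels. The detection rates and the 5% risk below are assumptions. The last column uses a normal approximation and ignores clustering.

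| d_I | d_C | Recorded ratio | Recorded, intervention (of 250) | Recorded, control (of 300) | Chance of nominal significance |
|---|---|---|---|---|---|
| 0.90 | 0.90 | 1.00 | 11.3 | 13.5 | 5% |
| 0.90 | 0.80 | 1.125 | 11.3 | 12.0 | 6% |
| 0.90 | 0.70 | 1.29 | 11.3 | 10.5 | 9% |
| 0.90 | 0.50 | 1.80 | 11.3 | 7.5 | 24% |

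For example, 250 × 0.05 × 0.90 = 11.25 and 300 × 0.05 × 0.70 = 10.5.

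**4. Size for adverse events.** If a share s of recorded intervention-arm events came only through Peer Navigators, the spurious rate ratio at equal risk is 1/(1 − s): 1.11 at s = 10% and 1.43 at s = 30%. If the PHQ-9 route is the only one counted, s = 0 and the ratio is 1.

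**5. A separate mechanism.** At the planned retention, PHQ-9 events at a 12-month visit, counted per randomised participant, would show 0.60/0.50 = 1.20 at equal risk, with no Peer Navigator reporting at all. Dividing by completed assessments removes that ratio but not a difference in reporters.

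**6. Effect on missing data.** At 5% risk there are 300 × 0.05 = 15 control deaths. Missing 20% to 30% of them leaves 3.0 to 4.5 unrecognised, or 2% to 3% of the 150 missing controls. In the intervention arm, 12.5 × 0.10 = 1.25, about 1% of the 100 missing.

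**The case against.** The case against is substantial, and much of it stands.

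- Section 21.2 is about archiving, and the quoted sentence is about telephoning when an email goes unanswered. It does not assign reporters exclusively. A reader might infer that Peer Navigators alone complete these forms. They do not: Research Assistants are named in the same sentence and work in both arms, and Service Managers can set a status change in motion in either arm (7.3).
- A reader might take 12.1 to mean that deaths are recorded only if known. The qualifier there attaches to cause and date, not to the recording of a death.
- Participant adverse events rest mainly on a question put to everyone assessed in both arms, and 12.1 denies any other traditional reporting. Section 12.2 is framed around what Peer Navigators themselves experience. A reader might infer that staff incidents inflate the participant counts. Nothing says so: a shared database is not a shared numerator, and 13.2 speaks of events per participant.
- Deaths are not a listed outcome, no dedicated between-arm test of harms is set out, and step 6 shows a minor effect on missing data, for which analyses under missing-not-at-random assumptions are already planned (14.6).
- The status query proposed below would not fully equalise knowledge, since 12.1 accepts that some participants will no longer be supported by the services at follow-up.

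What remains is that no control counterpart to the Peer Navigator is named, no independent check on deaths exists during the trial, and the four sections on adverse events do not fit together. Managers' ability to act in both arms is not a duty to report.

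**Conclusion.** The concern holds in a limited form. Followed as written, the plan can be expected to find deaths and other between-visit status changes more completely in the intervention arm. At equal true risk the recorded comparison may then lean against the intervention. The direction is plausible, but the size is unknown: the ratio is 1.00 if detection is equal, about 1.1 at 90% v 80% and about 1.3 at 90% v 70%. Every detection rate here is assumed.

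It would go too far to say that the safety comparison will tilt, or that it is uninterpretable. The protocol gives no detection rates, and its main adverse event source is common to both arms. For adverse events the problem is one of unreconciled text: a tilt arises only if Peer Navigator forms cover participant events and those forms enter the 13.2 counts. The primary outcomes are barely touched. This is a cheap improvement worth making, not a defect in the randomised comparison.

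**What to change.** 1. As each 6-, 12- and 15-month window closes, ask the same role in every cluster of both arms (the service manager or delegate) for the known status of each participant not assessed: alive, died or unknown. Report vital status unknown by arm.
2. In 13.2, base the between-arm adverse event comparison on events that researchers record at scheduled assessments. List participant events reported by Peer Navigators separately, as intervention-arm only.
3. Reconcile 12.1, 12.2, 13.2 and 21.2 on which adverse event forms exist, who completes them and which are counted. State that incidents experienced by staff are not participant adverse events.

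Cost: at least 20 clusters × 3 windows = 60 short queries, more where a cluster has several services, plus wording in the four sections. The load on service managers is small. Some asymmetry will remain for people who have left the services, but it will be visible by arm.

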## **22. Statement of indemnity**

The trial sponsor is the University of Stirling, and the University of Stirling will be liable for negligent harm caused to participants arising from the management of the research.

## **23. Trial organisational structure**

### **23.1 Responsibilities**

#### *Sponsor*

University of Stirling will sponsor the study and therefore has the responsibility for confirming there are proper arrangements to initiate, manage, monitor, and finance the trial.

#### *Project Management Group*

The strategic oversight of the trial will be provided by a Project Management Group, consisting of the grantholders (Chief Investigators and all other co-investigators), the Trial Managers (Stirling/Aberdeen), the Research Fellow (Stirling), Research Administrator, statistician and health economists and other senior members of the Trials Unit, and a representative from the study partner (The Salvation Army).

#### *Trial Management Group*

The management of the trial will be coordinated by a Trial Management Group consisting of the grantholders (Chief Investigators and a smaller group of co-investigators as required), the Trial Managers (Stirling/Aberdeen), the Research Fellow (Stirling), Research Administrator (Stirling), statistician, health economists and other senior members of the Trials Unit. This group will be responsible for making decisions concerning ongoing management of the trial and deal with any problems as they arise.

#### *Core Trial Group*

The day-to-day running of the trial will be the responsibility of the Core Trial Group which will consist of the Chief Investigators (Stirling/Aberdeen), the Trial Managers (Stirling/Aberdeen), Research Fellow (Stirling), Research Administrator (Stirling), and statistician.

## **24. Trial oversight**

### **24.1 Independent Trial Steering Committee**

A Trial Steering Committee (TSC), with independent members, will be established to oversee the conduct and progress of the trial. The membership and terms of reference of the Trial Steering Committee will be filed in the trial master file.

